## Abstract

**Background:**

The prevalence rate of attention-deficit/hyperactivity disorder (ADHD) within Western cultures is between 5% and 12%, and is the most common psychiatric illness among school-aged children, with an estimated 50% of these children retaining ADHD symptoms for the rest of their lives. Children with ADHD have lower blood levels of long-chain Poly Unsaturated Fatty Acids (LC PUFAs) compared with children without ADHD, and following PUFA supplementation, have shown improvements in ADHD-related symptoms. One highly promising marine based LC PUFA preparation is the Omega-3-rich Lyprinol/Omega XL which is a natural formulation containing standardised lipid extract of the New Zealand green lipped mussel (*Perna canaliculus*) known as PCSO-524® which contains a unique combination of free fatty acids, sterol esters, polar lipids and carotenoids. It is this unique combination of marine lipids that may assist in correcting the decreased levels of LC PUFA levels in children with symptoms of ADHD. The compound is a mixture belonging to a lipid group called sterol esters (SE). The fatty acids in the SE fraction are mainly myristic acid, palmitic acid, palmitoleic acid, stearic acid, oleic acid, linoleic acid, eicosapentaenoic acid (EPA), and docosahexaenoic acid (DHA). Lyprinol/Omega XL has previously been shown to contain a potent group of Omega-3 lipids that block the 5 - lipoxygenase metabolic pathway responsible for inflammation in the body.

**Methods:**

A randomized double blind placebo controlled trial will be utilized to assess the effects of 14 weeks administration of Lyprinol/Omega XL versus placebo in 150 children aged 6 to 14 years with high levels of hyperactivity and inattention. Additionally, a range of cognitive, mood and central electrophysiological measures will be undertaken during the 14 week supplementation trial. The primary outcome measure, the Conners’ Parent Rating Scales will be completed initially at baseline, then in weeks 4, 8, 10, 14 and then again at 4 weeks post-administration (week 18). The results will contribute to our understanding of the efficacy of marine based Omega-3 s with high anti-inflammatory actions on inattention and hyperactivity in children aged 6 to 14 years.

## Background and rationale

Developmental disorders can have detrimental effects on a child’s social, emotional and academic future. Attention-deficit/hyperactivity disorder (ADHD) is the most prevalent developmental disorder in school aged children [1-3]. The symptoms of ADHD include hyperactivity, impulsivity, and inattention and are common traits in other similar developmental disorders at both clinical and sub-clinical levels [4-6]. This subclinical group highlights an area of child mental health that is wide-spread and largely overlooked. A child’s ability to attend, recall and utilise learnt information inside and outside of the classroom is vulnerable to a number of environmental influences and genetic predispositions. Links to dysfunctions of neuro-circuitry [7,8], neuro-chemistry [9], developmental deviations [10,11] and neuronal maturation [12] have all been investigated as suspected causes for ADHD. One treatment model is based on the reduced levels of long chain poly unsaturated fatty acids (LC PUFAs) in the plasma of ADHD children compared to normals [6,13-15]. This has led to extensive research examining the efficacy of omega-3 supplementation as a natural alternative to methylphenidate (MPH e.g., Ritalin®) and other stimulant and non-stimulant pharmaceuticals [16,17].

### What is attention-deficit/hyperactivity disorder?

The prevalence rate of ADHD within Western cultures is between 5% and 12%, representing the most common psychiatric illness among school-aged children, with an estimated 50% of these children retaining ADHD symptoms into adulthood and for the rest of their lives [1,3] and less than 5% of this demographic attaining a university degree [18]. The disorder involves a child’s inability to maintain attention and focus and to remain calm, quiet and co-operative in both school and home settings. Symptoms of the disorder include inattention and/or excessive hyperactivity and impulsivity. A clinical diagnosis of the disorder involves one of three forms: *Predominantly Inattentive Type* (mainly symptoms of inattention), *Hyperactive-Impulsive Type* (mainly excessive behaviour related symptoms) or *Combined Type* (symptoms of both inattention and hyperactivity/impulsivity are clearly evident) [2].

Neurological causes of the disorder have been linked to dysfunctions of the Prefrontal Cortex (PFC) [7,8]. The PFC controls and moderates cognitive processes including executive functioning which includes decision making, planning and monitoring behaviours. Theories on the dysfunction of the neuro-circuitry within the prefrontal cortex have provided some insight into potential causes and are based on two developmental complications; maturational lag [12], or developmental deviation [10,11]. Depending on the severity of symptoms of the child, it has also been argued that this maturational lag in most children will gradually be reduced relative to healthy normal peers [19]. Developmental deviation has been found in electroencephalograph (EEG) studies revealing that despite age changes, ADHD symptoms and associated cognitive differences remain as maturation continues, suggesting an abnormal developmental path to peers [10,11]. The most common theories describing neurochemical causes of the disorder centre on low amounts of the catecholamine neurotransmitters dopamine and noradrenaline in the PFC [20,21]. There has been extensive research into these causes including genetic influences that predispose a child to deficits in dopamine (and serotonin) transmission [22]. Other causes have been attributed to exposure of the foetus/child to harmful agents in the prenatal, perinatal, postnatal and early childhood phases [23]. *In utero* exposure to excess alcohol, tobacco and lead have been linked to an increased risk of ADHD [4], while studies on diet have found that ADHD symptoms may become exacerbated when certain additives or food preservatives are consumed [24].

Stimulant medication such as methylphenidate (MPH e.g., Ritalin®), are considered to be beneficial for ADHD children as it is thought that administration of MPH increases levels of noradrenalin and dopamine in the PFC [1]. Animal models have demonstrated the efficacy of MPH by highlighting a specific mode of action of MPH in the dorsomedial PFC and linking this to cognitive performance in male Sprague–Dawley rats [25]. Some studies have also demonstrated effectiveness of MPH in treating those children with intellectual disabilities (IQ 30–69) and these disabilities have been known to increase the severity of ADHD symptomology [26]. Problems with the chronic use of these medications however, can lead to complications with appetite, trouble sleeping and increased levels of anxiety and a host of other unpleasant side effects [26-28]. Therefore it is not uncommon for parents to seek alternative treatments that do not have the same side effect profile as MPH for their children [29-31].

### The omega-3 model

Observations by Dyerberg and Bang (1986) found that the Eskimos of Greenland had low incidence rates of coronary heart disease due to their high fat diets dominated by the LC PUFA omega-3 [32]. This finding lead to further research into the actions of omega-3 s on cognitive, behavioural and cardiovascular functions. Children with ADHD have presented with lower levels of LC PUFAs in the blood compared with normal populations and following supplementation, have shown improvements in symptoms related to ADHD [15,17]. There are several reasons why these children may have insufficient LC PUFAs such as: low levels of the LC PUFAs obtained in the diet; the inefficient conversion of shorter chain PUFAs (SC PUFAs) into LC PUFAs; or the increased speed of metabolism of LC PUFAs [33]. Omega-3 s increase the malleability of neuronal cells, allowing more efficient nutrient exchange, increased cellular nourishment while also increasing fluidity of the blood [34,35]. Increased membrane fluidity is associated with faster neural transmission and more efficient biochemical performance [34]. Fontani et al. (2005) discovered that Omega-3 supplementation significantly improved higher brain functions including sense of well-being, reactivity, attention, cognitive performance, and mood in young healthy adults [36].

The New Zealand Green Lipped Mussel (*Perna canaliculus*) dates back to prehistoric times with coastal Maori folklore claiming that consumption of the mussels aided better health and fewer cases of arthritis than New Zealanders residing further inland [37]. In a trial designed in the 1960s to find cancer fighting therapies derived from various marine organisms, researchers found patients reported relief from symptoms of arthritis following the administration of the powdered form of *P. canaliculus*[38]. Since this time, research on *P. canaliculus* has shown benefits to cardiovascular functioning and anti-inflammatory processes [39-41]. Rheumatic disorders are second only to heart disease in the ageing population, making them one of the most prevalent and costly disorders in adults stimulating the increased research into *P. canaliculus*[42]. With inconsistent research results using non-steroidal anti-inflammatories (NSAIDs) [43] there has been significant use of natural medicines for rheumatic disorders [44]. The process of extracting the marine lipids from the *P. canaliculus* involves introducing tartaric acid to the freeze dried powder form under a patented mussel stabilization process [45]. This method was introduced following the inconsistent anti-inflammatory effects of *P. canaliculus* from batch to batch [46]. A recent systematic review on the freeze-dried powdered form of the *P. canaliculus* showed mixed evidence for its effects on osteoarthritis and rheumatoid arthritis, despite the preservation of its marine lipids [42].

### Lyprinol®/omega XL (PCSO-524®)

Lyprinol®/Omega XL is a unique oil-based form of *P. canaliculus.* A patented liquid carbon dioxide super critical fluid extraction process (PCSO-524®) is unique to Lyprinol®/Omega XL creating a highly condensed form of the marine lipids of *P. canaliculus*[47]. Studies on PCSO-524® have shown that this extract promotes anti-leukotriene production, which can reduce symptoms of asthma in a study population of young children [40]. It was this research that led to the confirmation of the safety and tolerability of PCSO-524® in a population of children as well as previous research demonstrating its efficacy and safety in adults [41,48,49]. The unique grouping of fatty acids in PCSO-524® has evolved as the most potent group of Omega-3 lipids in blocking the 5 - lipoxygenase metabolic pathway responsible for inflammation in the body [50]. It is this potent level of marine lipids that may assist in the decreased PUFA levels in children with symptoms of ADHD and similar developmental disorders and which is the major (but not only) mechanistic basis of the current clinical trial.

### Design

The study is a randomized, double-blind, placebo-controlled, 2-armed, parallel groups clinical trial with children and adolescents randomized to receive either 3 capsules (if less than or equal to 45 kg) or 4 capsules (if greater than 45 kg) of PCSO-524® or placebo.

### Study aims and hypotheses

The objective of this trial is to examine whether 14 week administration of a naturally occurring combination of omega 3′s improves a range of cognitive (measured with the COMPASS Cognitive Test Battery), mood (Brunel Mood Scales), behavioural (Conners’ Parent Rating Scale) and psychophysiological (electroencephalography and steady state topography) measures in children aged 6–14 years with symptoms of inattention and hyperactivity relative to placebo. It is anticipated that this project will conclude all testing in late 2013.

The primary aim of the current study is to examine the levels of hyperactivity, impulsivity and inattention in children aged 6 to 14 years of age before, during and after receiving a 14-week intervention of Lyprinol® compared to placebo. The primary outcome will be examining parental reports using the *Conners’ Parent Rating Scales −3* approximately every 4 weeks [51,52]. The Conners’ Parent Rating Scales (CPRS) were developed as a comprehensive checklist for acquiring parental reports of the basic presenting problems [52]. Secondary outcomes will also include the acquisition of resting state electroencephalography (EEG) in two states of eyes open and eyes closed. Changes in brain wave ratios in key areas of activity (prefrontal cortex) from baseline, week 8 and week 14 will also be examined to test the hypothesis that Lyprinol® will ameliorate the cortical hypoarousal that has been associated with ADHD [53] and increase the ratio of *alpha/beta* waves compared to *placebo*. Cognitive changes will be monitored using the Test of Variables of Attention (TOVA) as well as the Computerised Mental Performance Assessment System (COMPASS) [54]. Mood will be examined closely using the Brunel Mood Scale (BRUMs) for adolescents [55].

### Centres

All cognitive, mood and electrophysiological testing will take place within the Swinburne Centre for Human Psychopharmacology at Swinburne University in Victoria Australia. Additional CPRS will be issued to the parents of the participants who will be completing these questionnaires in the home environment in weeks 4, 10 and 18 (4 weeks post-administration of either Lyprinol or placebo).

### Participants

One hundred and fifty children aged between 6 and 14 years will complete either 14 week consumption of Lyprinol/Omega XL or placebo. This age range is one of the most common developmental stages for children to experience increased levels of hyperactivity, impulsivity and inattention and where 5-12% of children will receive a diagnosis of ADHD. The study was ethically approved by the Swinburne University Human Research Ethics Committee (SUHREC Project 2010/175) and all participants will provide written informed consent. All procedures will be conducted in accordance with the Declaration of Helsinki (2008) and the good clinical practice (GCP) guidelines. The trial has been registered with the Australian and New Zealand Clinical Trials Registry (ACTRN12610000978066).

### Inclusion and exclusion criteria

#### Inclusion criteria

Healthy, non-smoking males and females aged between 6 and 14 years; DSM-IV ADHD rating score above 15; Fluent in English; Parent/legal guardian to provide a personally signed and dated informed consent indicating that they have been informed of all pertinent aspects of the trial; the parent will then get verbal consent from the child.

#### Exclusion criteria

Medical diagnosis other than ADHD, Oppositional defiant disorder or similar behavioural disorders; Currently taking any medication (other than stimulants if a formal diagnosis of ADHD or other behavioural disorder is present); Current or history of heart disease or high blood pressure or diabetes; Health conditions that would affect food metabolism including the following: food allergies, kidney disease, liver disease and/or gastrointestinal diseases (e.g. Irritable bowel syndrome, coeliac disease, peptic ulcers); Pregnant or breast feeding; Unable to participate in all scheduled visits, treatment plan, tests and other trial procedures according to the protocol; Allergy to shellfish; Epilepsy or photosensitive.

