#### Randomization and safety

Randomization of participants to treatment groups will be determined by random allocation. All 150 participants will be assigned to treatment group A or B using a computer generated random number generator by a neutral third party. Eligible, recruited participants will be assigned a participant number. The treatment number that has been placed next to the participant’s number will be the allocated treatment for that individual. Blinding will be achieved by enlisting a person outside of the project to code the treatments, and maintain the key to this code until data collection is completed. An emergency code break envelope will be provided to the principle investigator which will only be opened in case of emergency. Participants’ parents will also be given a weekly symptom checklist to complete to monitor for any adverse events. Researchers will be blinded to the treatment conditions.

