#### Power and statistical analysis

The sample size for this study is 150 participants with 75 participants in each arm (Lyprinol vs Placebo). A power calculation to determine the sample size was performed using Gpower 3.12. Based on previous studies looking at omega-3 supplementation in children with ADHD such as Sinn & Bryan (2007) who had an *n* of 132 and were able to find statistical significance in terms of the CPRS [15], a small to medium effect size (F = .20) on the Conners’ was postulated for Lyprinol over placebo from baseline to week 18 over six time points (critical F = 3.92, with an alpha probability of 0.05 and beta power of 0.80). This provided a sample size of 118; with drop-outs being projects at approximately 20%, a sample of 150 participants was estimated. Repeated Measures ANOVAs with an *n* of 150 (75 per group) will allow the researchers to account for any confounding variables in the trial including within-group and between-group variability. Any heterogeneous variables showing statistically significant differences at baseline will be co-varied in order to negate their influence on the power of the study.

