## Conclusions

Attention-deficit/hyperactivity disorder (ADHD) is the most prevalent developmental disorder in school aged children [1,3]. The symptoms of ADHD include hyperactivity, impulsivity, and inattention. The prevalence rate of ADHD within Western cultures is between 5% and 12%, representing the most common neurodevelopmental disorder among school-aged children, with an estimated 50% of these children retaining ADHD symptoms into adulthood and for the rest of their lives [1,3] and less than 5% of this demographic attaining a university degree [18]. Interventions which are efficacious and which have no or little side effects are urgently required for both children and adolescents who fall within the clinical classification of ADHD and also who have high levels of the symptoms of inattention and impulsivity but who fall below the classification of ADHD. One treatment model is based on the reduced levels of LC-PUFAs in the plasma of ADHD children compared to normals [6,13-15,17]. This has led to extensive research examining the efficacy of omega-3 supplementation as a natural alternative to methylphenidate (MPH e.g., Ritalin®) and other stimulant and non-stimulant pharmaceuticals [16,17]. In the current study we will administer either placebo or a novel and patented marine lipid from the New Zealand Green Lip Mussel (PCSO-524®) to 150 children and adolescents with ADHD or high levels of inattention and hyperactivity for 14 weeks. A range of behavioural and neurophysiological measures will be undertaken. The results of the study will aid our understanding of the role of LC-PUFAs in improving behavioural, cognitive and physiological variables in children and adolescents and whether this intervention is efficacious.

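### Children on and off stimulants are pooled, no stimulant stratum is named, and the significance-triggered covariate rule would leave a moderate chance imbalance unadjusted

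*Protocol article*

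**What the plan says.** All of the following is in the protocol article.

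- **Inclusion criteria.** Entry rests on a symptom threshold, "DSM-IV ADHD rating score above 15". Neither a formal diagnosis nor a particular medication status is required.
- **Exclusion criteria.** A child is excluded if "Currently taking any medication (other than stimulants if a formal diagnosis of ADHD or other behavioural disorder is present". Stimulants are therefore the one medication allowed at entry, for diagnosed children.
- **Conclusions.** The sample is described as "150 children and adolescents with ADHD or high levels of inattention and hyperactivity for 14 weeks", so diagnosed and sub-threshold children are studied together.
- **Randomization and safety.** Participants are "assigned to treatment group A or B using a computer generated random number generator by a neutral third party". No stratification factor is named.
- **Power and statistical analysis.** There are to be "75 participants in each arm (Lyprinol vs Placebo". The adjustment rule is: "Any heterogeneous variables showing statistically significant differences at baseline will be co-varied".
- **Table 1.** The CPRS is taken at weeks 2, 4, 8, 10, 14 and 18. The Current Health & Medical Questionnaire is taken at weeks 1, 2, 4, 8, 10 and 14, but not at week 18.
- **Background and rationale.** Earlier research is described as "examining the efficacy of omega-3 supplementation as a natural alternative to methylphenidate". The Conclusions repeat this.

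**The concern.** Stimulants are aimed at the same symptoms that the CPRS measures, so stimulant use at baseline is a plausible prognostic factor. Which way it points is uncertain: medicated children may score better because they are treated, or worse because they were more severely affected.

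A prognostic factor known at screening is best balanced by design and kept in the model. The article instead makes adjustment depend on a significance test of the baseline difference. In a randomised trial that test asks whether chance produced the imbalance, which is already known. It takes no account of how strongly the variable predicts the outcome. It also lets the data choose the primary model, and it misses imbalances that are moderate in size but not significant.

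The second issue is interpretation. One pooled contrast answers a question about the mixture of children enrolled. It does not say whether an effect arises without stimulants, on top of them, or both.

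**Working it through.** **1. The plan's own figure.** Inputs from Power and statistical analysis: f = 0.20, six time points, alpha 0.05, power 0.80, critical F 3.92, N = 118 before drop-out, 150 enrolled. For the between-group term, λ = f²·N·m / [1 + (m − 1)ρ]. The article gives no ρ; I assume 0.5.

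- λ = 0.04 × 118 × 6 / 3.5 = 8.09, critical F(1, 116) = 3.92, power 0.805. The stated N reproduces.
- 118 / 0.80 = 147.5, so 148, consistent with 150.
- f = 0.20 for two groups is d = 2f = 0.40 SD.

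**2. Chance imbalance in stimulant use without a stratum.** The article gives no stimulant share p, so p is an assumption, shown as a range. With 75 per arm, SE = √[2p(1 − p)/75], by normal approximation.

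| Assumed p | SE | Significant beyond | P(difference ≥ 10 points) | P(≥ 10 points but not significant) |
|---|---|---|---|---|
| 20% | 0.065 | 12.8 points | 12.6% | 7.6% |
| 30% | 0.075 | 14.7 points | 18.1% | 13.1% |
| 50% | 0.082 | 16.0 points | 22.1% | 17.1% |

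The last column subtracts the 5% of trials in which the test is significant. At p = 30% a difference of exactly 10 points has z = 0.10/0.0748 = 1.34, a p-value of about 0.18, and so is not adjusted for.

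**3. What such an imbalance could do.** Assume that children on and off stimulants differ in CPRS level by 0.5 to 1.0 SD. A 10-point imbalance then shifts the arm difference by 0.10 × 0.5 = 0.05 SD to 0.10 × 1.0 = 0.10 SD, which is 12.5% to 25% of 0.40. The sign is unknown. Averaged over randomisations the shift is zero, so this is a loss of precision and not a systematic bias.

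**4. Pooling.** Pooled effect = p × (effect on stimulants) + (1 − p) × (effect off stimulants). At p = 30%, a pooled 0.40 fits 0.40 in both groups. It also fits 0 on stimulants with 0.40/0.70 = 0.57 off them. The pooled result alone cannot tell these apart.

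**5. Precision by stimulant status.** With 118 evaluable, p = 30% and the assumptions of step 1, SE = √[(2/n per arm) × 3.5/6].

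- On stimulants: about 17.7 per arm, SE 0.257, 95% half-width about 0.50 SD.
- Off stimulants: about 41.3 per arm, SE 0.168, half-width about 0.33 SD.

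These estimates would be descriptive only.

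**6. Stimulant changes during the trial (illustrative).** The article gives no change rates. Assume a change moves CPRS by 0.5 to 1.0 SD in that child.

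- Equal rates in both arms (5% to 20%): no bias; power goes from 0.805 to between 0.801 and 0.745.
- A net difference of 5 points between arms: a shift of 0.025 to 0.05 SD (6% to 12.5% of 0.40). If it dilutes, power is 0.75 to 0.69.
- A net difference of 10 points: a shift of 0.05 to 0.10 SD (12.5% to 25%). If it dilutes, power is 0.69 to 0.56.

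The shifts and dilution figures in the last two bullets are upper bounds for the assumed rates, because they hold the shift over all six ratings. A change made part-way through affects only the later ones.

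**The case against.** **The article is condensed.** Strata, a medication log and rules for on-study stimulant changes may sit in the full protocol or SAP. This stands. A reader might infer that allocation is simple and unstratified, or that stimulants are controlled only at entry. The article establishes neither: it says only that a random number generator assigns A or B, and the repeated questionnaire may capture medication. The covariate rule, however, is stated outright, and it is poor whatever the other documents contain.

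**Stimulant changes as treatment effect.** A reader might infer that starts, stops or dose changes will be counted as an effect of the capsule. In a randomised, double-blind, placebo-controlled trial, changes equally common in both arms add noise. Only a difference between arms biases the contrast. The most natural pattern is more starts or increases where behaviour stays poor, and if the product works that dilutes its effect.

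**Alternative to methylphenidate.** A reader might infer that pooling defeats the trial's purpose. That phrase describes prior research. The aim under Study aims and hypotheses is a comparison with placebo in children with symptoms, and pooling fits it. What remains is a limit on what can be concluded.

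**Baseline CPRS is measured.** A stable difference in level is already present at baseline and drops out of a change-from-baseline or group-by-time comparison. This reduces the stake in step 3. It does not remove it: the sample size reproduces as a between-group test over six points that include baseline, where a level difference would stay in.

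**Conclusion.** The point holds in a limited form. Children on stimulants are pooled with unmedicated and sub-threshold children, no stimulant stratum is named, and the stated rule adjusts only for significant baseline differences. With an assumed 30% on stimulants, an imbalance of 10 points or more arises in about 18% of trials (13% to 22% for shares of 20% to 50%). In about 13% of trials it reaches 10 points without triggering adjustment. The consequence for CPRS, 0.05 to 0.10 SD per 10 points, rests on an assumed prognostic effect and on an analysis that does not already remove baseline level.

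The placebo comparison is not invalidated. The documents do not show that stimulant changes will appear as treatment effect, and the figures for on-study changes are illustrative upper bounds. This is a modest weakness in precision and interpretability, worth correcting because correction is cheap.

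**What to change.** 1. Stratify the computer-generated list by stimulant use at baseline (yes/no). Screening must already establish this to apply the exclusion criterion.
2. Include that factor in the primary CPRS model regardless of any baseline test, and remove the significance-triggered rule.
3. Report the effect by stimulant status as a descriptive supportive analysis, and word the conclusion for the mixture actually enrolled.
4. Where the Current Health & Medical Questionnaire records medication, tabulate stimulant starts, stops and dose changes by arm. Extend the questionnaire to week 18, the last CPRS point.

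I would not make discarding ratings after a stimulant change part of this fix. It removes data informatively, possibly more in one arm.

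The cost is two lists instead of one for the third party, one model term, one more use of an existing questionnaire, and imprecise subgroup estimates. No clinical rule on stimulants is proposed.
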